### Outcomes and Outcome Measures

#### Overview

The outcome measures outlined in the following sections will be assessed at baseline and at 12, 26, and 52 weeks after initiating treatment. All outcome measures will be captured electronically and will not require a study or office visit.

The primary outcome of the proposed study will be the difference in mean MPR between the intervention and control groups during the 12-month study. The mean MPR will be calculated as follows:

MPR = number of days’ supply of medication obtained during observation period / total number of days in observation period.

If a participant discontinues therapy but initiates treatment with another eligible medication, the MPR will continue to be calculated. Any delay in initiating new treatment will be adjusted for the total number of days in the observation period (ie, if drug A is discontinued and drug B is started 2 weeks later, the observation period will be 365 – 14 = 351 days); for example, if a participant is prescribed oral mesalamine (1.2 g), 4 tablets daily, for 90 days (dispense 360) with 2 refills between months 6 and 12, the MPR would be 100%. Likewise, if a participant is prescribed ustekinumab 90 mg subcutaneous every 8 weeks (dispense 1 syringe) with 2 refills between months 6 and 12, the MPR would be 66%. Data on medication use will be self-reported by participants at each time point. However, we will randomly validate participant report via chart review of pharmacy data for 20% of the participants. Participants will report the date the medications of interest were filled as well as the number of days’ supply of medications filled. Self-reported adherence will be assessed with the Medication Adherence Report Scale-5 questionnaire (Table 2). Scores for each item are summed to give a total score, with higher scores indicating higher levels of reported adherence [33].

The secondary outcome of the proposed study will be the difference in health care use between the intervention and control groups during the 12-month study. For health care use, we will use a composite end point, including counts of hospitalizations, urgent care or emergency room visits, IBD-related surgeries, telephone calls (primary care and IBD provider), endoscopic procedures, imaging examinations, and blood and stool testing. We will also assess new prescriptions for corticosteroids (prednisone and budesonide) at each time point during the study period. The total events will be adjusted per 100 patient years of follow-up because the 2 groups will be unequal in number. In addition, we will evaluate each outcome individually. The relatedness of hospitalization and urgent care or emergency room visits to IBD will be determined as well. Information will be obtained from patient self-report at each assessment. This approach has been validated in patients with IBD using a modification of the Canadian Community Health Survey [34]. However, we will validate participant self-report via chart review for 20% of the participants, randomly selected.

**Table 2 table2:** Medication Adherence Report Scale-5 questionnaire.

Item	Scoring				
	Always	Often	Sometimes	Rarely	Never
I forget to take my medication	1	2	3	4	5
I alter my medication dose	1	2	3	4	5
I stop taking my medication for a while	1	2	3	4	5
I decide to miss out a dose of my medication	1	2	3	4	5
I take less medication than instructed	1	2	3	4	5

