### Study Conduct

Eligible patients will be approached by research staff at the time of routine clinical visits or via telephone and provide informed consent. All of the participants’ concomitant medications will be continued during the study. Corticosteroids will be tapered at the discretion of the investigator. Addition of new IBD medications will be allowed during the study. If the new medication is an eligible oral or subcutaneous addition to existing therapy, this will be tracked using the approach that was used to track the original medication during the initial treatment. If the new medication replaces the initial therapy, the replacement medication will be similarly tracked.

Participants will be randomized 2:1 to receive either remote monitoring or standard of care using a random permuted block design with randomly varied block sizes. Participants will be stratified based on study site and disease subtype (CD vs UC or indeterminate colitis). We chose to stratify on these variables because they could affect the response to the intervention; stratification will ensure balance of these covariates among the study groups. The randomization order will be computer generated, and group assignment will be made when a new participant is enrolled into the study by the clinical site. The site investigators and research staff will remain blinded to the randomization order. The participants and physicians will not be blinded to the group assignment; however, we will attempt to minimize measurement bias by collecting outcome data through electronic data capture directly from participants.

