For oral medications, mean adherence <80% in a 2-week period will trigger an alert. For subcutaneous medications, 2 missed doses of adalimumab and 1 missed dose of other biologics will trigger an alert. If alerts are triggered for nonadherence, a clinical nurse, pharmacist, or social worker will contact the participant to identify barriers to adherence; remediation will be initiated, if possible. For participants with CD, a PRO-2 abdominal pain score of 2 (moderate) or higher or a liquid stool frequency score of >4 will trigger an alert. For participants with UC or IBD type undetermined, a rectal bleeding score of 2 or a stool frequency score of 2 will trigger an alert (obvious blood most of the time or blood alone passes and stool frequency >2 stools more than normal, respectively). A clinical nurse will contact the participant if a symptom-based alert is triggered.

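### At a drug switch the MPR rule adjusts only the denominator, so supply of the stopped drug beyond its stop date still counts as possession and can offset missed supply of the replacement

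*Protocol article*

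**What the plan says.** The protocol article (Outcomes and Outcome Measures, Overview) fixes the primary endpoint: "The primary outcome of the proposed study will be the difference in mean MPR between the intervention and control groups during the 12-month study". MPR is days' "supply of medication obtained during observation period / total number of days in observation period".

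The same section sets a rule for switches. "If a participant discontinues therapy but initiates treatment with another eligible medication, the MPR will continue to be calculated". The accompanying adjustment concerns the observation period alone: "Any delay in initiating new treatment will be adjusted for the total number of days in the observation period". The worked case is: "if drug A is discontinued and drug B is started 2 weeks later, the observation period will be 365 – 14 = 351 days". That is one pooled period for both drugs.

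Study Conduct allows replacement therapy and adds: "If the new medication replaces the initial therapy, the replacement medication will be similarly tracked". It gives no rule for the numerator. Nowhere does the article limit the first drug's supply to the days before it was stopped, calculate MPR separately for each drug, or cap MPR at 100%.

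**The concern.** A ratio that continues across a switch needs both of its parts to follow the switch. Here the gap days leave the denominator, but supply of the stopped drug that nominally covers those days, and later ones, stays in the numerator. A participant who stops drug A partway through a fill carries the remaining days forward as credit. That credit can fill a real lapse in drug B, which is what the endpoint is meant to detect.

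Switching is foreseeable. All participants are starting a new therapy, replacement is permitted, and the article wrote a rule for it. The 20% pharmacy chart review would confirm that the fills took place, but not that the supply still applied after the switch. At stake is the accuracy of the primary endpoint in switchers and, if switching, leftover supply or lapses differ by arm, the comparison itself.

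**Working it through.** **The plan's own figure.** 365 − 14 = 351 days. It reproduces.

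**Inputs from the article.** Oral fills of 90 days (the mesalamine example in the Overview); one syringe per 8 weeks, that is 56 days (the ustekinumab example there); adherence of 0.90 in the intervention arm and 0.65 in control (Statistical Analyses). Switch rates, stop times and leftover days are not given, so every value for them below is an assumption.

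**One switcher.** Let L be the days of drug A supply beyond its stop date.
- As written: MPR = (all supply of A + supply of B) / 351.
- Truncated at the stop date: MPR = (supply of A up to its stop date + supply of B) / 351.
- Difference = L / 351, or 1/351 = 0.28 points per day.

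*Illustration.* Drug A is filled for 90 days on day 0 and stopped on day 30, so L = 60. Drug B starts on day 44 and is due for 365 − 44 = 321 days. Suppose 60 of these are not supplied: 321 − 60 = 261.
- As written: (90 + 261)/351 = 100%.
- Truncated: (30 + 261)/351 = 83%.
- Difference: 60/351 = 17 points.

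*Second illustration.* Drug A is filled on days 0 and 90 (180 days) and stopped on day 100, so L = 80. Drug B starts on day 114, is due for 251 days, and lacks 80, so 171 are supplied.
- As written: (180 + 171)/351 = 100.0%.
- Truncated: (100 + 171)/351 = 77.2%.
- If drug B is fully supplied: (180 + 251)/351 = 122.8% as written, against 100% truncated.

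*No effect.* Stopping on day 180 after two 90-day fills gives L = 0.

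**Average switcher, no cap, stops spread evenly within fills (assumed).**
- 90-day fills: 45/351 = 12.8, about 13 points.
- 56-day fills: 28/351 = 8.0 points.

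**One arm's mean.** Overstatement = switch rate × mean L / 351. For assumed rates of 10% to 40% and mean L of 15 to 80 days, it runs from 0.10 × 15/351 = 0.4 points to 0.40 × 80/351 = 9.1 points.

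**Difference between arms, no cap.** With assumed switching of 30% (intervention) and 20% (control) and equal mean L:
- 90-day fills: (0.30 − 0.20) × 12.8 = +1.3 points.
- 56-day fills: (0.30 − 0.20) × 8.0 = +0.8 points.
- Equal switching: 0.

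**Difference between arms, MPR capped at 100%.** Assume the same 30% and 20%, L uniform on 0 to 90 days, drug A fully supplied up to its stop, 321 drug B days, and 0.90 and 0.65 read as the share of drug B days supplied. The overstatement is then the smaller of L and the drug B shortfall g. Its mean is g − g²/180 when g is below 90, and 45 otherwise.
- Intervention: g = 0.10 × 321 = 32.1; mean 32.1 − 32.1²/180 = 26.4 days; 26.4/351 = 7.5 points; × 0.30 = 2.25.
- Control: g = 0.35 × 321 = 112; mean 45 days; 12.8 points; × 0.20 = 2.56.
- Net: 2.25 − 2.56 = −0.3 points, against the intervention.

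With 180 drug B days instead, g is 18 and 63 days, the mean overstatement is 16.2 and 40.95 days, and the net is 1.38 − 2.33 = −0.95 points.

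**The case against.** **The article does not say in words that leftover supply is kept.** Derivation details of this kind are often left to an analysis plan, which is not shown. The first part is true: the result is inferred from a formula based on supply obtained, a pooled 351-day period, and a switch rule that changes the denominator only. But the article does set out how switches are handled for the primary endpoint, and it adjusts one side of the ratio. The rule applied as written gives a wrong value, which is more than an omitted detail.

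**MPR measures supply obtained, not use.** The Background section itself says that such records do not show intake. That is fair as a general limit. It does not explain why days after a drug's stop should count toward possession of its replacement.

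**A 100% cap would deal with it.** In part. A cap removes the overstatement when drug B is fully supplied (122.8% becomes 100%). It does nothing when leftover days fill a real lapse, as in the case that scores exactly 100% instead of 83%. That case pairs 60 leftover with 60 missed days to make the masking plain; it is not a typical participant.

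**An injected syringe leaves nothing over.** Correct. With one syringe per dose, the excess is days' supply overlapping the replacement rather than unused product. The arithmetic is the same.

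**The stronger reading: the rule favours the intervention.** A reader might infer this because symptom alerts belong to that arm ("A clinical nurse will contact the participant if a symptom-based alert is triggered") and could bring more or earlier switches. The documents do not support it. They give no switch rate. Control participants also have scheduled and as-needed visits and calls (Control Group). The expected better outcomes (Study Expectations) could mean fewer switches with the intervention. Under a cap, the arm with more lapses has more to mask, and the sign reverses above even with switching assumed higher in the intervention arm.

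**Conclusion.** The defect holds as mismeasurement of the primary endpoint in switchers who stop a drug before its supply runs out. The size for one participant is firm: 0.28 points per leftover day when the period is 351 days and no cap applies. The averages of about 13 points (90-day fills) and 8 points (56-day fills) rest on evenly spread stops and no cap.

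The effect on the difference between arms is unknown in size and direction. The values of +1.3 and −0.3 points show only how assumptions move it, and both are small beside the planned contrast of 0.90 and 0.65 (25 points, if those rates are read as mean MPR). The point therefore does not show that the trial would reach a false conclusion. It shows an avoidable error in the endpoint rule that is worth correcting before MPR is derived.

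**What to change.** Add one sentence to the MPR definition in Outcomes and Outcome Measures, Overview: at a switch, the days' supply of the stopped drug counts only up to its stop date, any remainder is excluded from the numerator, and the replacement counts from its first fill, with the same rule in both arms.

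The cost is small. Fill dates and days' supply are already reported. The stop and start dates are already needed to remove the gap from the denominator, although the Overview does not name the stop date among the items participants report, so the data form should be checked for it. Treatment is unaffected. The downside is a slightly lower MPR among switchers.

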At the time of taking a medication dose, participants will scan the label with their mobile phone to verify that they are taking the medication. Upon scanning, participants will immediately receive a notification on their device indicating that the label was successfully scanned and that their medication adherence was updated in their profile. Each day that a medication is due to be taken, participants will receive a reminder through SMS text message notifying them of their medication schedule for the day. If participants fail to scan the label at a given time (as determined by their specific medication regimen), they will receive an SMS text message at the end of the day with a link to respond to a survey that captures reasons for nonadherence.

Participants will also complete a PRO-2 assessment at baseline and then monthly for the entire 12 months of the study triggered by the Tappt system through an HTML link sent to patients by SMS text message [31,32]. For participants with CD, the PRO-2 assessment includes abdominal pain and liquid stool frequency. For participants with UC or indeterminate colitis, the PRO-2 assessment includes rectal bleeding and stool frequency. The research team will also be able to send the PRO-2 survey to patients at any given time, at their discretion, if patients are experiencing a flare or at the time of a change in medication dose. Items for the PRO-2 assessment vary based on disease type (refer to the Outcomes and Outcome Measures section).

Clinical teams can review their participants’ data in real time through the secure cloud-based provider-facing Tappt portal. To reduce monitoring burden among clinical teams, the system’s algorithms prompt automated email alerts to the clinical team when participants’ adherence or PROs fall below predetermined thresholds, when a participant’s regimen is approaching refill date, or when a participant reports an error on their profile. These alerts can support clinical teams in following up with patients in a timely manner to reduce risk for poor outcomes (Figure 1).

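### The ustekinumab example for the primary endpoint (66%) does not follow from the stated MPR formula, which gives about 61–62%, and the formula as printed lets on-time refilling score above 100%

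*Protocol article*

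**What the plan says.** In the protocol article, Outcomes and Outcome Measures, Overview, the primary outcome is the between-group difference in mean MPR over 12 months. The formula is "MPR = number of days’ supply of medication obtained during observation period / total number of days in observation period". The period is counted in calendar days: a two-week gap between drugs shortens it from 365 to 351 days.

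Two worked examples follow, the second presented as the same calculation as the first:

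- For "oral mesalamine (1.2 g), 4 tablets daily, for 90 days (dispense 360" tablets), the article states "with 2 refills between months 6 and 12, the MPR would be 100" per cent.
- For "ustekinumab 90 mg subcutaneous every 8 weeks (dispense 1 syringe"), it states "with 2 refills between months 6 and 12, the MPR would be 66" per cent.

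Participants report fill dates and days' supply. Under Statistical Analyses, the two group means are compared by t test. Under Study Conduct, if an eligible drug is added, "this will be tracked using the approach that was used to track the original medication". No upper limit on the MPR is printed, and no rule is given for supply that extends past the end of the period.

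**The concern.** Worked examples are what programmers and site staff tend to follow when a definition leaves room for doubt. Here the formula and one of its two illustrations disagree, so a reader cannot tell whether a syringe is scored in days, in doses or in nominal months. Tablets and injectables are pooled in one mean, so the unit should be the same for both.

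The second issue is the numerator. It counts supply by when it was obtained, not by when it covers the participant. A fill just before the end of the period earns full credit although most of it covers days outside the period. Scores above 100% then enter the mean and can mask gaps in other participants.

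**Working it through.** **Inputs.** From Outcomes and Outcome Measures, Overview:

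- Mesalamine: 360 tablets at 4 per day = 90 days per fill.
- Ustekinumab: 1 syringe every 8 weeks = 56 days per fill.
- Both examples: 2 refills between months 6 and 12.
- Full observation period: 365 days.

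The article does not give the length of months 6 to 12 in days. The assessments at weeks 26 and 52 (Study Schedule) are 26 × 7 = 182 days apart. I take 180 to 184 days as the plausible range, and I read 2 refills as two fills inside the window.

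**Formula.** MPR = fills × days' supply per fill ÷ days in window.

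**The plan's own figures**

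| Window (days) | Mesalamine, 2 × 90 = 180 | Ustekinumab, 2 × 56 = 112 |
|---|---|---|
| 180 | 100.0% | 62.2% |
| 182 | 98.9% | 61.5% |
| 182.5 | 98.6% | 61.4% |
| 184 | 97.8% | 60.9% |
| Stated | 100% | 66% |

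Mesalamine is reproduced exactly at 180 days and to about 1 point at 182. Ustekinumab is not reproduced: the gap is 66 − 62.2 = 3.8 to 66 − 60.9 = 5.1 points.

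**Where 66% could come from**

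- Two of three expected doses, equivalent to a 168-day window: 112/168 = 66.7%. At 168 days mesalamine becomes 180/168 = 107.1%.
- Eight weeks taken as two months (60 days): 120/180 = 66.7%, or 120/182 = 65.9%.
- Counting an initial fill as well does not help: 3 × 56 = 168, and 168/182 = 92.3%. Mesalamine would then be 270/182 = 148.4%.

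With 56 days per syringe, no single window gives both printed figures.

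**No limit on supply, over 365 days**

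- 90-day fills on days 0, 90, 180, 270 and 360: 5 × 90 = 450, and 450/365 = 123.3%. The last fill covers 5 days inside the period and 85 outside it.
- If that fifth fill is a week late it falls on day 367, outside the period: 4 × 90 = 360, and 360/365 = 98.6%. One fill therefore moves a participant by 90/365 = 24.7 points.
- 56-day fills on days 0, 56, …, 336: 7 × 56 = 392, and 392/365 = 107.4%. The last fill covers 29 days inside and 27 outside.

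Counting only supply inside the period gives 360 + 5 = 365 days and 336 + 29 = 365 days, so both on-time participants score 100%.

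**Offsetting in a mean.** A participant with 450 days' supply and one with 280 (280/365 = 76.7%) average (450 + 280)/(2 × 365) = 100%. With the first limited to 100%, the mean is (100 + 76.7)/2 = 88.4%.

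**The case against.** The strongest reply is that little is wrong. The formula itself is clear, the data it needs are collected, and the 66% is a slip of 4 to 5 points in an illustration that plays no part in the sample size. A months convention (6/6 and 4/6) yields both examples with one rule. Caps and overlap rules commonly sit in a full protocol or SAP, which is not shown here.

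Much of this stands:

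- A reader might infer that both examples are wrong. The mesalamine figure is right for a 180-day half-year.
- A reader might infer that tablets are scored by days and injectables by doses. Dose counting is only one possible origin of 66%; the two-month reading is another. Neither, however, is the stated formula applied to an 8-week interval.
- A reader might infer bias towards the intervention, because the system alerts when a participant's "regimen is approaching refill date". Those alerts go to the clinical team, prompting timely refills is part of the intervention, and late fills occur in both arms. No difference between arms is shown.
- A reader might infer that the supply of two concurrent drugs is summed. The article says that an added drug is tracked, not how the two are combined.
- Six 8-weekly fills scoring 336/365 = 92% is not an error: 29 days really are uncovered.

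The reply does not remove the second issue. The article prints a specific formula and works through switches and gaps, and that formula credits supply beyond the period. If the full protocol or SAP already limits it, the article needs only to agree with that text.

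**Conclusion.** The concern holds in a limited form. The ustekinumab figure contradicts the stated formula by about 4 to 5 points, assuming 56 days per syringe and a half-year of 180 to 184 days; the mesalamine example stands. As printed, the formula also gives scores of 107% to 123% for ordinary on-time refilling, and these can offset non-possession in the group mean.

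The swing of about 25 points from one fill is for a single participant. It is tempting to set it against the gap between the assumed adherence rates of 0.65 and 0.9, but it is not an estimate of bias in the treatment comparison. The documents give no distribution of fills by arm from which to calculate one. The sample size of 123 is unaffected by the example.

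**What to change.** - Correct the ustekinumab example to about 62% (112/182).
- State the window length in days, and that every drug is scored in days' supply.
- For the primary analysis, count only supply falling within the observation period and cap each participant's MPR at 1.0. Report the uncapped MPR as a sensitivity analysis.
- State how concurrent tracked drugs are combined into one MPR per participant.

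This keeps MPR as the endpoint; a full change to a covered-days measure goes further than the problem requires. Fill dates and days' supply are already collected, so the cost is wording and minor programming. Some individual values will become lower. The rules should be fixed before outcome data by arm can influence the choice.

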The variance in adherence is in part due to inconsistent measurement. Objective and validated approaches include pill counts, refill counts, and pharmacological or biochemical markers; subjective approaches include validated measures, visual analog scales, and patient interviews. Some approaches may work better in certain settings, given that they measure adherence in different ways and at different time points [10]; for example, although validated measures are effective in clinical trials, they can be burdensome and time consuming in real-world practice. Furthermore, they do not capture day-to-day variability in adherence because the adherence measure summarizes medication-taking behaviors over a designated period [3]. Similarly, pharmacy records and insurance databases provide data that can be used to calculate MPR and percentage of days covered by the prescriptions, but they do not provide information on medication intake patterns and do not capture use of samples [10,11]. Patient interviews are the most efficient way to gather a complete picture of patient adherence, but they can be unreliable, given that patients tend to overestimate their adherence [10].

In recent years, electronic- and virtual-based platforms have been developed to monitor adherence routinely and guide appropriate interventions. These remote therapy monitoring (RTM) systems include electronic pill caps, electronic pill and needle boxes, bidirectional SMS text message reminders, and patient-facing mobile apps [10,12-14]. Although some of these have been successful at monitoring and improving adherence, they are limited by their battery requirement and cost as well as the survey fatigue of respondents. Furthermore, these solutions and apps collect data inconsistently and are not synchronized with clinical teams’ workflows in a real-time manner to identify patients at risk for nonadherence and drive actionable follow-up.

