### Study Population

Patients will be recruited for this study from 5 clinical centers at the University of Maryland School of Medicine, University of Cincinnati School of Medicine, NYU Grossman School of Medicine, University of North Carolina School of Medicine, and Vanderbilt University School of Medicine.

Inclusion criteria will include (1) aged ≥18 years; (2) documented IBD based on usual diagnostic criteria, including clinical symptoms and findings from endoscopy, radiology studies, and histology [30]; (3) initiation of treatment with a new oral or subcutaneous treatment for IBD; (4) access to a smartphone with a reliable data plan or Wi-Fi access; and (5) ability to understand the protocol and provide informed consent in English. Exclusion criteria will include (1) inability to speak and read English or comply with the study protocol; (2) the presence of an ileostomy, colostomy, ileoanal pouch anastomosis, or ileorectal anastomosis; (3) initiation of oral corticosteroids only without concurrent use of an oral or subcutaneous maintenance therapy; (4) imminent surgery within the next 60 days; (5) history of short bowel syndrome; or (6) uncontrolled medical or psychiatric disease.

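### The MPR numerator is defined as supply obtained, but only fills are recorded, and the pharmacy-data check shares the gap for samples

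*Protocol article*

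**What the plan says.** All references are to the protocol article.

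- **Endpoint** (Outcomes and Outcome Measures, Overview): "The primary outcome of the proposed study will be the difference in mean MPR between the intervention and control groups during the 12-month study".
- **Formula** (same section): "MPR = number of days’ supply of medication obtained during observation period / total number of days in observation period". The numerator is worded as supply *obtained*.
- **Inputs** (same section): "Participants will report the date the medications of interest were filled as well as the number of" days supplied by those fills. These are self-reported. The two worked examples in that section also count refills only.
- **Check** (same section): "we will randomly validate participant report via chart review of pharmacy data for 20% of the participants".
- **Known limit of pharmacy data** (Introduction, Background): pharmacy and insurance records allow MPR to be calculated, "but they do not provide information on medication intake patterns and do not capture use of samples".
- **Population** (Study Population): every participant enters at "initiation of treatment with a new oral or subcutaneous treatment for IBD".
- **Intervention arm only** (Intervention Group): after a nonadherence alert, a nurse, pharmacist or social worker "will contact the participant to identify barriers to adherence; remediation will be initiated, if possible". Alerts also go to the clinical team near a refill date.

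**The concern.** The formula and its inputs do not describe the same quantity. Samples are supply obtained, but they are not fills. The article names this weakness of pharmacy-based MPR and then chooses self-report, a source that could avoid it. It nevertheless describes the self-report as limited to fills.

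The validation step does not close the gap. If a sample is missing from both the participant's report and the pharmacy data, the two agree and no discrepancy appears. Good agreement in the roughly 25 checked participants (0.20 × 123 = 24.6) would then be reassuring without being informative on this point.

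At stake is the level of the primary endpoint for anyone who receives samples. If sample use differed between arms, the between-arm difference would be affected too. Supply that is never asked about may not be recoverable later.

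**Working it through.** **Inputs from the article.** Observation period 365 days (the figure used in the article's drug-switch example); formula as quoted; planned rates 0.65 and 0.90; allocation 2:1; N = 123.

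**Assumed, because the article gives no figure.** Sample days *d* = 14 or 28 inside the observation period; share of participants given samples; standard deviation (SD) of MPR.

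**1. The plan's own figures.**
- Mesalamine example: 2 refills × 90 days over half a year is 180/182.5 = 98.6%, given as 100%.
- Ustekinumab example: 2 refills against 3 eight-week intervals is 2/3 = 66.7%, given as 66%. By days it would be 112/182.5 = 61.4%.
- Both examples put only refills in the numerator.
- The sample size of 123 (41 + 82) reproduces with a two-sided two-proportion formula without continuity correction. This point does not change it. It is used here only for its 25-point gap (0.90 − 0.65) as a yardstick.

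**2. Largest loss for one fully supplied participant.** Leaving *d* days out of the numerator costs at most *d*/365.
- 14/365 = 3.8 points
- 28/365 = 7.7 points (scored 92.3%)

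Against full coverage of 100%, the whole of this is lost only if the last fill is truncated at the end of the period.

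**3. Loss when the last fill is not truncated.** The formula as written counts all supply obtained in the period. Start fills when the samples run out:
- 28 sample days, 90-day fills on days 28, 118, 208 and 298: 4 × 90 = 360; 360/365 = 98.6%
- 28 sample days, 30-day fills from day 28 to day 358: 12 × 30 = 360; 98.6%
- 14 sample days, same two patterns: 360/365 = 98.6% again

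The shortfall from 100% is 1.4 points, because supply left over from the last fill offsets the uncounted samples.

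**4. Start of the period.** If observation began at the first fill, samples used before it would fall outside the period and cost nothing. The article times assessments from treatment initiation, which suggests that such days count, but it does not state the start date of the MPR period.

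**5. Arm means, using the upper losses from step 2.** Shift = share × *d*/365.
- 25% of an arm affected: 1.0 point (14 days) or 1.9 points (28 days)
- 50% affected: 1.9 or 3.8 points

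If the shares are equal in both arms, the shifts subtract out of the difference in means.

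**6. Spread.** With an assumed SD of 0.25 and sample use independent of true MPR, 28 days in half the participants gives √(0.25² + 0.0767² × 0.5 × 0.5) = 0.253. The added noise is negligible.

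**7. Bias if use differs by arm.** Bias = difference in shares × *d*/365.
- 10 percentage points, 14 days: 0.10 × 3.84 = 0.4 point
- 20 percentage points, 28 days: 0.20 × 7.67 = 1.5 points

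That is 1.5% to 6.1% of the 25-point yardstick, again using the upper losses.

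**The case against.** **The form itself is not shown.** The article summarises in one sentence what participants report, and the full protocol may word the item more broadly. This tempers the point. But the article does state the inputs, and as stated they are narrower than the numerator, so asking for alignment is not a complaint about omitted detail.

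**The Background criticism concerns pharmacy and insurance records, not self-report.** That is correct. It applies directly to the validation step, and to the self-report only because that report is described as limited to fills. The check is a chart review, and a chart might mention samples, so it would be too strong to say the check cannot detect them.

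**Larger losses are sometimes inferred.** A reader might add clinic-administered doses or bridging supply and reach 15.3 points for one uncounted eight-weekly dose (56/365). The article mentions neither source. Even for one such dose, six later fills give 336/365 = 92.1% under the formula as written. The same caution applies to 3.8 and 7.7 points, which are ceilings and not fixed costs.

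**Bias against the intervention is not shown.** A reader might infer that staff remedy nonadherence with samples, so that successful help lowers measured MPR in that arm alone. The article does not say that remediation includes samples, and the control group may also have nurses, pharmacists and social workers. What stands is only that unequal use is possible in an unblinded trial with alerts in one arm.

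**Flagging of over-reports.** A reader might also expect the check to mark honest sample reports as over-reporting. Under the stated inputs samples are not reported, so there is nothing to flag. The issue would arise only once the question is widened.

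**Conclusion.** The mismatch is real and concerns the primary endpoint: the numerator is supply obtained, the stated inputs are fills, and the check relies on data that the article says miss samples. A participant who receives samples can be scored below the supply actually held, and the check as described would probably not reveal it.

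For an assumed 14 to 28 sample days inside a 365-day period, the loss runs from about 1 point to at most 3.8 to 7.7 points. Where in that range it falls depends on refill timing, the start of the period and truncation of the last fill.

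The effect on the treatment comparison is smaller and conditional. Similar use in both arms largely cancels. If use differed by 10 to 20 percentage points, the bias would be about 0.4 to 1.5 points at the upper losses. The documents give neither the frequency of samples nor any difference by arm, so neither the presence nor the direction of bias can be asserted. This is a cheap improvement of minor to moderate priority.

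**What to change.** - At weeks 12, 26 and 52, ask for days' supply obtained from any source, including samples, with the date and the source of each item.
- Count all of it in the numerator, by the same rule in both arms, so that the data match the formula.
- In the 20% check, compare only pharmacy-sourced items with pharmacy records, so that a correctly reported sample is not read as a discrepancy.
- When making the change, confirm when the observation period starts and whether the last fill is truncated at its end, since these decide how much samples matter.

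Cost: one extra field on an existing electronic form and a small burden on participants. It should be in place before recruitment starts. The sample size is unchanged.
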